### Cohort profile

Using data collected at enrolment, we will describe non-participation among women recruited to the study (ineligible, non-consent, declined to recruit others), the range and mean size of the sample recruited through the network-based (RDS) strategy, and present recruitment trees by site. We will describe unweighted characteristics of study participants and describe the number with missing data for the outcomes as recommended by the STROBE-RDS extension [24]. Although we cannot present non-participation among women not attending study sites, we will describe the mean and range of women who did not recruit peers by site and ask women recruited into the study to estimate how many women they tried to recruit but who refused. We will report any recruitment challenges in line with the STROBE-RDS extension [24].

### Assessing balance across sites

Using enrolment data, we will describe characteristics of the YWSS recruited into the DREAMS+PrEP and non-DREAMS comparison cohorts. To assess whether there is any imbalance across the two cohorts in risk factors for HIV, we will conduct a comparative analysis of the socio-demographic characteristics, sexual behaviours of the YWSS recruited to the impact evaluation, and prevalent and recent infection. Where there is evidence of imbalance in factors likely to influence HIV risk, we will adjust for these individual-level factors in our analysis of the primary outcome as described below.

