### Primary outcome measurement

The primary outcome is HIV incidence over the 24 months following enrolment into the study, the numerator will be the number of new infections among young women testing HIV-negative at enrolment, the denominator the person-years of follow-up. Person-years of follow-up for each YWSS will be calculated as: 1) time between the first HIV negative test at enrolment and an HIV negative test at 12 months and 24 months; or 2) the mid-point between an HIV negative test and an HIV positive test. If a participant is lost to follow-up (LTFU), the participant will be censored at last HIV-negative test.

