### Sample size justification

DREAMS aims to reduce HIV incidence among AGYW by 40%. In the absence of a robust estimate of HIV incidence among the target population, we used data from the *Sisters* programme and the MTN-020 Dapivirine vaginal ring trial to determine the required sample size [9, 30]. A cohort analysis of *Sisters* programmatic data estimated that HIV incidence was 10.8% (95%CI: 8.1–16.1) among FSW aged 18–25 years [9]. In the ASPIRE trial, HIV incidence among women aged 18 to 45 was 4.5 per 100 person-years in the placebo arm, 6.2 per 100 person years in the placebo arms in South Africa, 2.6 in Malawi, Uganda and Zimbabwe [30]. Relative to the target population in our study, women in the ASPIRE trial might have been at lower risk of HIV, with only 7% reporting transactional sex in the previous year. Based on these estimates and assuming individual-level analysis, we assume that incidence among YWSS in the absence of DREAMS+PrEP is between 5.0 and 8.0 new infections per 100 person-years. We also anticipate that, at the point of enrolment, 20% of YWSS will test HIV positive and that 30% of YWSS will be LTFU over the 24-month period. Based on these estimates, we will recruit 1200 YWSS in the DREAMS+PrEP sites and 1200 in non-DREAMS sites to have sufficient person-years of follow-up to have 80% power to detect a reduction of 40% or more in incidence after 24-months at the *p* = 0.05 level (Table 1).

**Table 1 Tab1:** Study power to detect a 30–50% reduction in HIV incidence in DREAMS+PrEP cohort compared to incidence in a comparison cohort with at least 690 YWSS followed up over 24 months (1500–1380 person-years follow-up/cohort)

HIV incidence in comparison cohort	Reduction in HIV incidence in DREAMS+PrEP cohort					
	50%	40%	30%	50%	40%	30%
	1500pyrs follow-up per cohort			1380pyrs follow-up per cohort		
5.0	94	77	49	92	75	46
6.0	96	85	59	96	82	55
7.0	98	90	66	98	87	62
8.0	99	93	72	99	91	67

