We recognise that retention of the YWSS recruited into the cohorts may prove challenging, as such our sample size calculations assume a 30% LTFU over the 24-month study. Furthermore, individuals LTFU may differ in the two groups, leading to bias estimates of HIV incidence. We opted for a cohort design rather than repeat cross-sectional surveys as we are interested in the impact of DREAMS+PrEP among YWSS referred to and offered DREAMS+PrEP services. We recognise that both design options have limitations. Repeat cross-sectional surveys, however, would suffer from issues of temporality, we would not be able to explore individual-level changes over time, and women recruited at successive surveys may have had no exposure to DREAMS+PrEP. Through our cohort study design, YWSS will be referred to and offered DREAMS+PrEP services dependent on need. Our study will therefore allow us to understand women’s level of engagement and reasons for non-engagement with DREAMS.

The DREAMS package of interventions aims to reduce HIV incidence by 40% among AGYW. As such, our study is powered to detect a 40% difference in HIV between the DREAMS+PrEP and non-DREAMS comparison cohorts. This is a large reduction in incidence. If DREAMS+PrEP reduces incidence by 40% we may be able to detect this difference, if levels of LTFU and HIV prevalence at enrolment are as hypothesised, but reductions lower than 40% may not be detected with the proposed sample size. PrEP efficacy studies have shown up to 67% reduction in HIV among sero-discordant couples and young men and women in sub-Saharan Africa [1, 37, 38]. Sub-group analyses suggest efficacy is higher with increased levels of adherence [1, 37]. An offer of PrEP alongside interventions to support retention in or return to school, and improve access to HIV testing, STI screening and treatment among other services are likely to have a large impact on these women’s lives, their access to services and their risk of HIV infection. Should this study be underpowered, it can still provide evidence critical to understanding whether and how DREAMS+PrEP changed young women’s lives and to informing how to provide this underserved and vulnerable population with access to HIV prevention and care services within a broader social support package.

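### Balance is judged, and adjustment triggered, among all women recruited, but the rate ratio comes only from HIV-negative women with a later test, so confounding in that smaller set can be missed

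*Protocol article*

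**What the plan says.** Under Assessing balance across sites, the set compared is everyone recruited: "Using enrolment data, we will describe characteristics of the YWSS recruited into the DREAMS+PrEP and non-DREAMS comparison cohorts". The characteristics compared end with "sexual behaviours of the YWSS recruited to the impact evaluation, and prevalent and recent infection", so HIV-positive women are in the table. The same paragraph gives the consequence for the primary outcome: "Where there is evidence of imbalance in factors likely to influence HIV risk, we will adjust for these individual-level factors in our analysis of the" (the sentence then names that outcome).

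Under Primary outcome measurement, the set is narrower: "the numerator will be the number of new infections among young women testing HIV-negative at enrolment, the denominator the person-years of follow-up". A woman lost to follow-up is censored at her last negative test. If that was the enrolment test, she gives no person-time.

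Under Stages of primary outcome analysis, the rate ratio is weighted by the inverse of reported network size and, in phase two, adjusted for potential confounders. No other set is named in which those confounders are identified. The article reports how many women are retained and their follow-up time by group, but no comparison of their characteristics.

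The planning inputs are that "20% of YWSS will test HIV positive and that 30% of YWSS will be LTFU over the 24-month period". The Discussion concedes that "individuals LTFU may differ in the two groups" and that this may bias the incidence estimates, without attaching a check to it.

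**The concern.** The rule that decides adjustment looks at one set of women and the estimate comes from another. Two steps separate them: removal of women already infected, and loss before any repeat test. Either can change the mix of risk, and can do so differently by group. The recruits' table may then show no difference while the women who generate the rate ratio differ in risk, and a factor that should enter phase two would not be flagged.

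This matters more here than in a randomised trial. Allocation was not random, there are only six sites, and inference rests on plausibility, so the balance assessment is a main piece of evidence for comparability.

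**Working it through.** **1. Reproducing the plan's figures.** Inputs from Sample size justification: 1200 recruited per group, 20% HIV-positive, 30% lost over 24 months.

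- HIV-negative at enrolment: 1200 × 0.80 = 960.
- Followed to 24 months: 960 × 0.70 = 672, giving 672 × 2 = 1344 person-years.
- Table 1 states at least 690 women and 1380 person-years. The difference is 18/690 = 2.6%.
- Power as Φ((e0 − e1)/√(e0 + e1) − 1.96), with e0 and e1 the expected infections, matches all 24 cells of Table 1 within two points. Example: 6.0 per 100, 1380 person-years, 40% reduction gives e0 = 82.8, e1 = 49.7 and power 82%, as stated.

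The sample size is not in question.

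**2. Size of the gap between the two sets.** Of 1200 women in the balance table, 240 (20%) cannot contribute because they are HIV-positive. If every lost woman was never retested, the analysed set is 672/1200 = 56%. If every lost woman was seen at 12 months, it is 960/1200 = 80%. The truth lies between.

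**3. Can balance among recruits coexist with imbalance among those analysed?** All inputs in this step are assumptions. In both groups 30% of recruits are high-risk (15 per 100 person-years) and 70% low-risk (3 per 100). Both have had three years at risk before enrolment, with the same past hazard in both groups. In the DREAMS+PrEP group, 45% of high-risk and 25% of low-risk HIV-negative women are never retested; in the comparison group, 30% of each. The programme has no effect.

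- High-risk and HIV-negative: 0.30 × e^(−0.45) = 0.191. Low-risk and HIV-negative: 0.70 × e^(−0.09) = 0.640. Prevalence is 1 − 0.831 = 17% in both groups.
- DREAMS+PrEP retested: 0.191 × 0.55 = 0.105 and 0.640 × 0.75 = 0.480, so the high-risk share is 0.105/0.585 = 18.0%. Overall loss is 1 − 0.585/0.831 = 29.6%.
- Comparison retested: the share stays at 0.191/0.831 = 23.0%, with loss 30%.
- Incidence = 15 × share + 3 × (1 − share): 5.16 and 5.76 per 100 person-years. Rate ratio = 5.16/5.76 = 0.90.

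| High-risk share | DREAMS+PrEP | Comparison |
|---|---|---|
| All recruited | 30% | 30% |
| HIV-negative at enrolment | 23.0% | 23.0% |
| HIV-negative and retested | 18.0% | 23.0% |

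Prevalence and overall retention look alike. Only the last row shows the difference.

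**4. Other assumed patterns.** A risk factor is present in 40% of recruits in both groups, with 20% prevalence and 30% loss overall. With s1 and s0 the analysed shares and k the rate for the factor relative to its absence, the null rate ratio is (1 + (k − 1)s1)/(1 + (k − 1)s0).

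- Loss 40% vs 23% by risk level in one group, 30% throughout in the other: shares 34% vs 40%; rate ratio 0.96 (k = 2) or 0.94 (k = 3).
- Prevalence 35% vs 10% by risk level in one group, 20% throughout in the other: shares 32.5% vs 40%; rate ratio 0.95 or 0.92. Total prevalence is equal, since 0.4 × 0.35 + 0.6 × 0.10 = 0.20.
- Loss 45% vs 20% in one group and 15% vs 40% in the other: shares 31% vs 49%; rate ratio 0.88 or 0.83.

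These show that the mechanism works. They do not estimate its size in this study.

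**The case against.** **The columns of a baseline table are ordinary SAP content, and a SAP is promised.** This is true of the layout. But the article goes further: it names the set compared and makes adjustment follow from it. That is a stated rule, and the SAP should correct it rather than inherit it.

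**Phase two adjusts for potential confounders and does not forbid a wider set.** This stands. A reader might infer that confounding will be missed; the text supports only that it can be.

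**The planned comparison of prevalence would raise an alarm.** Sometimes it would. Take the assumptions of step 3, but with past hazard 1.5 times higher in the DREAMS districts and no difference in loss by risk. Prevalence is then 17% vs 24%, which with 1200 per group gives z of about 4.1 and would be seen. It does not help where loss is the cause, or where total prevalence is equal but differently composed.

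**A reader might infer a predictable bias towards benefit, because DREAMS districts were chosen partly on HIV burden.** The documents do not support this. In the scenario just described the null rate ratio is 0.94, and 0.84 with the step 3 loss pattern added, but both need the higher hazard to stop at enrolment. If it persisted, the no-loss figure would be about 1.5 × 0.94 = 1.4, in the opposite direction.

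**A reader might also infer that the balance table is unweighted while the analysis is weighted.** The words "We will describe unweighted characteristics of study participants" belong to the Cohort profile section. The balance section is silent on weights, so no contradiction is shown.

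**Differential loss is already acknowledged, and adjustment cannot fully repair it.** Both parts are right. Moreover, retention comes after exposure and may be affected by the programme, so choosing covariates only from the retested set would be debatable. This shapes the fix.

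**Conclusion.** The point holds in a limited form. As written, the adjustment trigger is applied to all recruits, while the rate ratio rests on 56% to 80% of them. Quoting 56% alone would understate the analysed set, because women last tested at 12 months also give person-time. A factor balanced among recruits can be unbalanced among the women analysed and so escape adjustment.

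The document gives no basis for the size or direction of any resulting bias. Under the assumptions of step 3 the null rate ratio is about 0.90, and the patterns in step 4 give 0.96 to 0.83. For scale, the study is designed to detect a rate ratio of 0.60. No stated figure in the plan is wrong. The change is worth making because it costs little and the comparability evidence carries much of the inference.

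**What to change.** In Assessing balance across sites, or in the SAP before it is finalised:

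1. Make the comparison that triggers phase-two adjustment among women HIV-negative at enrolment, using the inverse-network-size weights of the primary analysis.
2. Keep the comparison of all recruits, including prevalent and recent infection, as evidence on whether recruitment reached similar populations in the two groups.
3. Add a parallel column for HIV-negative women with at least one follow-up HIV test. Adjust also for enrolment risk factors that become unbalanced there, in addition to those found under item 1 and not in place of them.
4. State that item 3 addresses selection from loss only in part.

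In the step 3 example only the column in item 3 reveals the imbalance; in the prevalence example of step 4 the column in item 1 does so. Both are therefore needed.

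The cost is two more columns in a planned table, a few sentences of text and possibly a few more covariates. No new data are required, and the sample size does not change.

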Across sub-Saharan Africa, adolescent girls and young women (AGYW) are at disproportionately higher risk of HIV than older females and their male peers [1, 2]. This increased risk is driven by a combination of biological, behavioural and structural factors [3]. At highest risk of infection are young female sex workers (FSW) and other young women who sell sex (YWSS) for financial or material resources [4]. Relative to older FSW, young FSW and YWSS aged under 25 years are at increased risk due to economic vulnerability, sexual partnerships with older men more likely to than younger men to have prevalent infection, and reduced skills in condom use negotiation [5–8]. Limited access to available health services for fear of stigma and discrimination further increases their risk of HIV and other health outcomes [5, 7]. In Zimbabwe, our experience is that YWSS, those under 25 years as well as those who have most recently begun sex work, may not identify as sex workers. Consequently, they are less likely to access sex work specific services [4, 9]. Younger FSW are also less frequently recruited to research studies of FSW [10, 11]. As such, YWSS are particularly vulnerable to new infection as well as being hidden and complex to conduct evaluation studies with. We anticipate that their risk of new HIV infection is very high; our estimates among young FSW suggest an incidence perhaps as high as 10% per year [9].

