### Key considerations for study design

We seek to estimate the impact of the DREAMS+PrEP intervention on HIV incidence among YWSS aged 18–24. The DREAMS+PrEP intervention includes identifying high risk women, referral for an offer of PrEP for those testing negative, and referral to other DREAMS interventions, depending on need and availability, that will support use and adherence through a variety of behavioural and structural interventions. This impact evaluation has four main design challenges. First, it was not possible to randomise study sites to receive the DREAMS intervention. DREAMS districts were selected through country-level consultation and based on population of AGYW and HIV burden. Second, YWSS, the target group for this evaluation are a “hidden” population for which a sampling frame does not exist. Third, there are few intervention districts, and 80% of the intended beneficiaries that fall within our target group will be recruited from only two districts. Fourth, there are numerous providers and the strategies to identify, reach and refer YWSS to services is complex.

Our overall approach to these design challenges is to: 1) use existing data (from the *Sisters* programme) to select comparison sites comparable to the DREAMS+PrEP sites in factors known to influence HIV risk; 2) leverage the use of the network-based (respondent driven) strategy that is being used to identify and reach YWSS, refer these YWSS to services, in order to recruit them into the impact evaluation, and repeat this process in the non-DREAMS comparison sites; 3) take a cohort analysis approach to compare HIV incidence among YWSS in the DREAMS+PrEP sites with YWSS in the non-DREAMS comparison sites, and collect data on recent infection and risk factors for HIV incidence at enrolment in support of an adjusted analysis; 4) embed a process evaluation within the impact evaluation to seek to understand intervention implementation, and document any contextual factors determining the success or failure of delivery of intervention components.

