### Statistical analysis

We aim to adhere to the transparent reporting principles of TREND [22]. In addition, we will report on items essential to the network-based (RDS) recruitment as per the STROBE-RDS extension [23]. We will finalise a statistical analysis plan before data collection at 24-months is complete.

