### Stages of primary outcome analysis

We will adopt a transparent and simple cohort approach to the analysis of the primary outcome. Our approach to inference will consider whether it is plausible that DREAMS+PrEP had an impact on HIV incidence among the target population [28, 29].

We will conduct our primary analysis in three phases. Each stage aims to build the strength of the evidence base of a plausible causal impact of DREAMS on HIV incidence. In phase one, we will take an individual-level cohort analysis approach. At 24-months, we will describe the number of women retained in the cohort and summarise follow-up time (average and total) in the DREAMS+PrEP and comparison sites. We will describe HIV incidence at 24 months in the DREAMS+PrEP and comparison groups with associated 95%CI. We will also describe site-specific estimates of incidence. Using Poisson regression, we will compare the incidence rates at 24-months across the two groups expressed as an unadjusted rate ratio with associated 95%CI presented. To account for the RDS design, we will weight the data by 1/self-reported degree of social network.

The unadjusted rate ratio is subject to confounding by risk factors for HIV that are differential across the two groups in the absence of random allocation and the small number of sites. In phase two, we will estimate a rate ratio adjusted for potential confounders. We will present the adjusted rate ratio with associated 95%CI.

In the third phase, we will assess whether there is evidence for an association between individual-level exposure to DREAMS+PrEP interventions and HIV incidence. For example, we will compare the risk of HIV infection between women self-reporting that they are adherent to PrEP and women who did not take PrEP. We will specify the exact measures of exposure after the year 1 data have been collected, without reference to the outcome data and before the final follow-up.

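### Phase-two adjustment is triggered by observed imbalance at enrolment, so strong HIV risk factors with modest imbalance can be left out of the adjusted rate ratio

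*Protocol article*

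**What the plan says.** Under *Assessing balance across sites*, the protocol article plans an enrolment comparison of the two cohorts on socio-demographic characteristics, sexual behaviour, and prevalent and recent infection: "To assess whether there is any imbalance across the two cohorts in risk factors for HIV, we will conduct a comparative analysis". The result decides the adjustment: "Where there is evidence of imbalance in factors likely to influence HIV risk, we will adjust for these individual-level factors". That sentence points forward to the primary analysis.

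Under *Stages of primary outcome analysis*, the article accepts that adjustment is needed: "The unadjusted rate ratio is subject to confounding by risk factors for HIV that are differential across the two groups". It then says: "In phase two, we will estimate a rate ratio adjusted for potential confounders". No factor is named as always included, no selection rule other than the imbalance trigger appears, and no measure or threshold of imbalance is given.

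*Key considerations for study design* says the study will "collect data on recent infection and risk factors for HIV incidence at enrolment in support of an adjusted analysis". On timing, *Statistical analysis* says: "We will finalise a statistical analysis plan before data collection at 24-months is complete".

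**The concern.** The bias from leaving out a factor is governed by two things: how far its distribution differs between the cohorts, and how strongly it predicts HIV. The rule looks at the first and uses the second only as an entry condition (the factor must be likely to influence risk). Among plausible risk factors, one that triples the hazard but differs by 3 percentage points may be left out, while a weaker one that differs by 6 points is adjusted for.

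Allocation was not random, so imbalances may be systematic, and failing to detect one is not evidence that it is harmless. Phase two is the only regression adjustment for confounding. What its covariate set omits remains in the adjusted rate ratio, in a direction that cannot be known in advance: it could hide part of a real reduction or exaggerate one. The rule also means that the adjusted model cannot be stated until the enrolment data have been examined.

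**Working it through.** **Inputs from the article (*Sample size justification*).** "we will recruit 1200 YWSS in the DREAMS+PrEP sites and 1200 in non-DREAMS sites"; 20% HIV-positive at enrolment; 30% lost over 24 months; comparison incidence 5.0–8.0 per 100 person-years; target reduction 40%; 1380–1500 person-years per cohort (Table 1).

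**Assumptions not in the article.** Binary risk factor with prevalence p = 25% or 30%; rate ratio 3 with HIV; imbalance judged by a two-sided test at p<0.05; design effect (DEFF) for the network sample 1 or 2.

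**1. The plan's own figure.** Table 1 gives 82% power for a 40% reduction at 6.0 per 100 and 1380 person-years. Expected events are 1380 × 0.06 = 82.8 and 82.8 × 0.6 = 49.7. The standard error of the log rate ratio is √(1/82.8 + 1/49.7) = 0.179. Power = Φ(0.511/0.179 − 1.96) = 81.2%. All 24 cells agree within 2 points, so the power table is not at issue.

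**2. Largest imbalance that goes unflagged.** HIV-negative women per cohort: 1200 × 0.8 = 960. Limit d = 1.96 × √(DEFF × 2p(1−p)/960).

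| p | DEFF 1 | DEFF 2 |
|---|---|---|
| 25% | 3.9 points | 5.5 points |
| 30% | 4.1 points | 5.8 points |

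**3. Bias from one omitted factor.** Bias = (1 + 2(p+d))/(1 + 2p).
- At the limits above, p = 25%: 1.052 (DEFF 1) and 1.073 (DEFF 2); p = 30%: 1.051 and 1.072.
- A 3-point imbalance at p = 30%: 1.66/1.60 = 1.037. A 5-point imbalance: 1.70/1.60 = 1.062.
- Over prevalence 20–50%, imbalance 3–5 points and rate ratio 2–4, the bias is 2% to 9%.

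**4. How often the rule catches the factor.** At p = 30% and 960 per cohort, a true 3-point imbalance reaches p<0.05 in 29% of studies and a 5-point imbalance in 65%. If all 1200 recruited women are compared, the figures are 35% and 74%.

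**5. Average effect of the rule.** Simulation: 300 replicates per row, 960 women per cohort, 30% lost, comparison incidence 6 per 100 person-years, true rate ratio 0.60, p = 30%, every factor with rate ratio 3 and all imbalanced in the same direction.

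| Factors | Imbalance | Unadjusted | Imbalance-selected | All factors | Selected ÷ all |
|---|---|---|---|---|---|
| 1 | 3 points | 0.627 | 0.616 | 0.602 | 1.02 |
| 1 | 5 points | 0.618 | 0.587 | 0.578 | 1.02 |
| 3 | 3 points | 0.680 | 0.639 | 0.598 | 1.07 |
| 3 | 5 points | 0.714 | 0.613 | 0.586 | 1.05 |
| 5 | 3 points | 0.760 | 0.687 | 0.608 | 1.13 |
| 5 | 5 points | 0.841 | 0.657 | 0.606 | 1.08 |

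The last column compares models fitted to the same simulated data and is steadier than the separate columns, which carry simulation noise.

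Not all of the five-factor excess is confounding. Confounding alone would put the unadjusted value at 0.60 × 1.0375⁵ = 0.721 for 3 points, against 0.760 simulated, and at 0.60 × 1.0625⁵ = 0.812 for 5 points, against 0.841. The remainder is consistent with the pull towards 1 that comes from leaving strong predictors out of a rate model. Full adjustment removes both.

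**6. Events available.** At a 40% reduction and 1380 person-years: 1380 × 0.05 × 1.6 = 110, up to 1380 × 0.08 × 1.6 = 177.

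**The case against.** The strongest reply is that the article does not say other factors are excluded. It promises adjustment where imbalance is seen, speaks more widely of potential confounders in phase two, and leaves the covariate list to the analysis plan. This stands in part: a list and a threshold are ordinary analysis-plan content, and their absence is not the point. But the trigger is stated, it refers forward to the primary analysis, and nothing there replaces it. A plan that follows the article would inherit it.

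Several stronger readings are tempting and are not supported:
- **A p-value rule.** No test or threshold is stated. Another criterion, such as a standardised difference, would change the figures above but not the principle.
- **Covariates chosen to suit the result.** Selection uses enrolment characteristics, not incident infections, and only factors judged likely to influence HIV risk. It is data-dependent, not outcome-driven.
- **Phase two as the sole defence against confounding.** Comparison sites were chosen for comparability, and the same network recruitment is used in both groups. These give some design-stage protection.
- **A built-in difference in who is recruited.** *Background* says of young women who may not identify as sex workers: "Consequently, they are less likely to access sex work specific services". A reader might infer that the comparison cohort will lack such women. However, coupons bring women to the study site in both groups, and referral to services follows. The remark concerns use of services, not response to a study coupon.
- **Multiplying the threshold bias over several factors.** That requires every factor to sit at the limit, to be missed, and to act in one direction. At the limit each is missed about half the time, so three independent factors would all be missed about 1 time in 8. The simulation averages over this and gives less.

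Sampling error is also larger than any of these biases: at 6.0 per 100, a 40% reduction and 1380 person-years, the 95% interval is the estimate multiplied or divided by exp(1.96 × 0.179) = 1.42. But that error is reported in the interval, and residual confounding is not.

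**Conclusion.** The point holds as a weakness in a stated method, and its size is modest. Conditioning adjustment on observed imbalance can leave out strong HIV risk factors with modest imbalance.

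One missed factor matters little. Several acting together could move a true rate ratio of 0.60 to between about 0.61 and 0.69 after imbalance-selected adjustment (three or five factors in the simulation), or by a similar proportion the other way. Those values depend on assumed prevalence, strength of association, a 5% significance trigger and a common direction; none is given in the article. The conclusion that the rule is the wrong criterion does not depend on them. The sample size and Table 1 are unaffected.

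**What to change.** Replace the trigger in *Assessing balance across sites*. Phase two should adjust for a confounder set chosen on prior knowledge from what the enrolment questionnaire records: for example age, education, self-identification as a sex worker, duration of selling sex, partner numbers and condomless sex. Fix the set before any outcome data are seen, including 12-month HIV results, and keep it whatever the observed balance. Further factors found to be imbalanced may be added; otherwise the balance table is descriptive.

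The cost is one reworded sentence and a list in the analysis plan. No new data are needed and the sample size does not change. The downside is a few degrees of freedom against roughly 110–177 expected infections.
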